**Participant Recruitment and Selection**

Recruitment through our recruitment methods requires the individual to complete an online screening survey. It will be up to the person to take the initiative to complete the online screening survey on their own time from their location of choice. Beyond study staff, no one will know who completes the online screener unless the participant chooses to share the information. The screener itself is maintained in a secure database, REDCap, and only study staff will be able to access their responses. Additionally, prospective participants can close out the screener at any time. Moreover, study questions are not designed to be harmful and instead focus on data collection. Recruitment involving former or current study participants who consented to recontact for future studies will also be contacted. We will only contact those who permitted contact on their consent forms through their approved email address or phone number.

Participants who meet the initial screening criteria via the online survey will be scheduled for an Orientation Video Call (e.g., Zoom or Teams, per the participant's preference). During the orientation, eligibility will be verified. A private location will be encouraged for the Orientation Zoom/call.

# **6. Cost to Participants and Incentives to Participate**

**Potential Costs/Reimbursements**

Costs associated with taking part in the study include any cell phone plan or WIFI related costs (needed to complete surveys online and participate in study calls). If any medical issues arise as a result of the study, these would be covered by the participant and not the study.

All nicotine pouch and nicotne replacement therapy costs will be covered by the study.

**Incentives**

Participants will be provided with a ClinCard for incentives. $25 will be loaded to the participant’s ClinCard for each survey/assessment completed and a $25 bonus will be added for completing all 5 surveys/assessments. Participants may also receive $10 for each smoker they refer who completes the online and verbal screenings. They may refer up to 5 smokers. The total incentive is up to $200.

# **7. Compensation for Research-Related Injury**

If a participant suffers an injury from participating in this study, they should notify the researcher or study doctor immediately, who will help determine if they should obtain medical treatment.

The cost for this treatment will be billed to the participant or their medical or hospital insurance. The Ohio State University has no funds set aside for the payment of health care expenses for this study.

# **8. Informed Consent Process**

| Specify the consent process(es) to be used for the study. Check all processes that apply. For any waivers or alterations, complete the applicable appendix. |
| --- |
| Informed Consent with Written Signature (e.g., on paper)  Informed Consent with Electronic Signature  Note: If the method used to obtain electronic signatures does not qualify as a legally valid signature, also check “Waiver of Consent Documentation.” See guidance provided by the [Office of Technology and Digital Innovation](https://u.osu.edu/esigforinformedconsent/).  Waiver of Consent/Parental Permission Documentation  Deception (i.e., procedure in which investigators deliberately mislead participants during research by withholding information or providing false information).  Note: If this is selected, also check “Waiver or Alteration of the Consent Process.”  Waiver or Alteration of the Consent Process  Waiver of the Parental Permission Process |

Upon confirmation of eligibility and willingness to participate, participants will receive an oral and written explanation of the study. Study staff will review the consent document with participants and answer any questions the participants may have. Participants will demonstrate that they understand key aspects of the study by verbally answering questions from study staff about participation (e.g., “Can you tell me what the risks of participation are?”). The voluntary nature of the study and the participant’s right to withdraw at any time will be stressed during the consent process.

Participants will electronically sign the consent form only after both the participant and the study staff member are confident that the participant understands their participation and the risks associated with participating. The informed consent agreement will be collected by IRB-approved study personnel. Consent signatures will be collected electronically via REDCap ***(Consent Form)*** and stored electronically in the secure REDCap database***.***A copy of the informed consent document will be provided to the participant electronically ***(Copy of Consent Message)*** and a blank hard copy will be included in the study kit. All participants will provide their consent before any study procedures are performed.

We aim to minimize coercion or undue influence by:

- Educating the participant as much as possible and providing ample time to ask questions and contemplate prior to completing consent
- Incentive amounts are nominal
- Although we are using addictive products, the products are commercially available, and all available evidence suggests they are much less harmful than cigarettes.

# **9. Privacy of Participants**

Recruitment through our recruitment methods requires the individual to complete an online screening survey. It will be up to the person to take the initiative to complete the online screening survey on their own time. Beyond study staff, no one will know who completes the online screener unless the participant chooses to share the information. The screener itself is maintained in a secure database, REDCap, and only study staff will be able to access their responses. Additionally, prospective participants can close out the screener at any time. Moreover, study questions are not designed to be harmful and instead focus on data collection. Recruitment involving former or current study participants who consented to recontact for future studies will also be contacted. We will only contact those who permitted contact on their consent forms through their approved email address or phone number.

All Zoom/phone calls will be encouraged to take place in a private setting for both the staff member and participant. All surveys are sent to the participant's email and/or texted to the cell phone number provide by the participant.

# **10. Confidentiality and Management of Study Materials**

|  | Y | N | Comments |
| --- | --- | --- | --- |
| Does the research involve obtaining and storing participants’ data and/or biospecimens for future, unspecified, research? |  |  | If yes, complete the Repositories appendix. |

Confidentiality will be maintained by all study staff along with the use of a secure study database. All lab personnel and study staff will complete HIPAA and CITI trainings, human subjects protection training and responsible conduct of research training. Phone scripts will be developed to ensure the subject is in a private environment where they are comfortable sharing personal information during the Orientation Zoom/call. REDCap, will store participant data. A subject ID will be assigned to each participant in order to code study data. Multiple levels of security clearance are required before entering the REDCap system and only approved study personnel will have access to this data.

All data will be collected and stored electronically in the secure database, REDCap. Subjects’ first and last names, phone numbers, and addresses will be coded and not linked with downloadable study results. Data will be stored under a code, not first or last name. Primary research data should be retained for a minimum of five years after final project closeout.

Research will be conducted in accordance with CTR policies and IRB regulations. Questions will be directed to OSU IRB representatives and S/AEs will be reported per IRB policy. All participant data is stored electronically within REDCap with no hardcopy records.

The data quality control process involves randomly sampling completed records each quarter to assess their completeness and accuracy. This ensures that all required fields are filled out properly and that no critical data is missing. Additionally, discrepancies or inconsistencies are flagged for review and correction. The process also includes regular audits to verify the integrity of the data and ensure compliance with study protocols. By systematically monitoring data quality, we can identify potential issues early and maintain the reliability of the study results.

Study procedures, collecting iCO measurements, completing and logging phone calls, assembling and shipping kits, gift card administration, and other procedures will be thoroughly explained in the study procedure manual.

For the iCOquit app, the participant will need to create an account with their email and a password. The app will ask for name and age. There are questions about their smoking habits, but they are optional (cigarettes smoked a day, price per pack, minutes before first cigarette of the day, etc). The parent company, Covita, does not have access to the information/data that is collected by the app.

# **11. HIPAA Research Authorization**

| Is individually identifiable Protected Health Information (PHI) subject to the [HIPAA Privacy Rule](https://go.osu.edu/hipaaprivacysummary) requirements to be accessed, used, or disclosed in the study?  No  Yes |
| --- |
| If PHI is accessed, used, or disclosed, specify how authorization requirements will be met (check all that apply). For any waivers or alterations, complete the applicable appendix. |
| Written Authorization  Partial Waiver (for identification and recruitment purposes only)  Full Waiver (authorization will not be obtained)  Alteration (written authorization will not be obtained or all required elements will not be included) |

# **12. Reasonably Anticipated Benefits**

Participants are not expected to benefit from this project; however, it is possible they may consider reducing their tobacco intake or switching to a less harmful product as a result of their interactions with research staff or the study product(s).

Participants assigned to the Control group will receive combination NRT, the leading forms of pharmacotherapy for smoking cessation, free of charge. Participants assigned to the ONP condition will receive a product that is likely much less harmful than conventional cigarettes to completely switch to for 12 weeks, free of charge. In general, this study will provide a benefit to the public as the findings will be reported to health officials and the US FDA to inform effective tobacco control policies. In an ever-changing marketplace of tobacco and nicotine products, ONPs are non-combustible and tobacco-leaf-free alternatives to cigarettes, although the potential for them to serve as substitutes is largely untested. The current trial will provide information about whether ONPs can be an effective method to reduce the harms of cigarette smoking among rural Appalachian adults who smoke. Participants may indirectly consider quitting tobacco products or choosing a harm reduction product as a result of their involvement with this investigation though this is not a study objective. Through their contributions to science, subjects provide insight into a novel tobacco product that could benefit public health and alleviate the burden of tobacco use.

In general, this study will provide a benefit to the public as the findings will be reported to health officials and the US FDA to inform effective tobacco control policies. In an ever-changing marketplace of tobacco and nicotine products, ONPs are non-combustible and tobacco-leaf-free alternatives to cigarettes, although the potential for them to serve as substitutes is largely untested. The current trial will provide information about whether ONPs can be an effective method to reduce the harms of cigarette smoking among rural Appalachian adults who smoke. Through their contributions to science, subjects provide insight into a novel tobacco product that could benefit public health and alleviate the burden of tobacco use.

# **13. Risks, Harms, & Discomforts**

Every effort will be made to minimize risks to participants. Participation in surveys involves minimal risk. However, there is a possibility of loss of confidentiality or privacy. Additional potential risks include: the risk of smoking cigarettes, using oral nicotine pouches or nicotine replacement products, possible interference with your plans to quit smoking, and the potential for developing side effects from the study products. These side effects may include hiccups, gum irritation, mouth sores, nausea or upset stomach, headache, sore throat, cough strange or vivid dreams, trouble sleeping, dizziness, heartburn, and redness, swelling, burning or irritation at the patch site. Stop using the study product and seek medical care if  you experience irregular heartbeats or palpitations, severe chest pain or tightening, painful mouth sores or blisters that do not resolve, severe skin irritation or discoloration, symptoms of an allergic reaction, or symptoms of nicotine overdose (like extreme paleness, cold sweat, nausea, abnormal salivation, vomiting, abdominal pain or severe headache, disturbed hearing or vision, dizziness, mental confusion, or weakness).

Additional details:

1. Use of nicotine replacement therapy. For our study, participants assigned to the control group will be given nicotine replacement therapy (combination transdermal and short-acting lozenge). In both instances, there is no link between NRT and congenital anomalies.

1a. Nicotine lozenge: In a recent trial of placebo vs. single vs. multiple medications for smoking cessation, the three most common adverse events within the lozenge group were 1) nausea: 7.8%, compared to 4.4% within placebo group, 2) mouth/throat irritation: 6.7%, compared to 3.3% within placebo group, and 3) hiccups: 6.2%, compared to 0.3% within placebo group. All other adverse events occurred <5%.

1b. Nicotine patch. The most common side effects from nicotine patch are skin irritation, insomnia, and headache or nausea. In an early but seminal placebo-controlled test of patch, there were few systemic side effects of patch use: 21% vs. 15% of smokers in the patch and placebo groups respectively reported a side effect during the treatment period. The most frequent symptoms with the patch as compared with the placebo patch were headache (4 vs. 4 percent), nausea (4 vs. 1 percent), and vertigo (4 vs. 0 percent). Transient mild itching was reported by 14% of the subjects in the patch group and 1% in those in the placebo group.

2. Use of oral nicotine pouches. ONPs are not combusted and do not contain tobacco leaf, and as a result, they deliver lower levels of toxicants than cigarettes. A recent study reported adverse events following administration of a 4mg ONP, 4mg NRT lozenge, and 4mg NRT gum. The incidence of product-related adverse events was lowest in the ONP group (12.1%) followed by NRT gum (12.5%) and NRT lozenge (30.3%). Overall, 97% of AEs were mild, with 6% of participants reporting dizziness after ONP use (the most common AE) and no reports of nausea or throat irritation following ONP use. No serious AEs were reported in the ONP group. ONP use in pregnant women has not been studied, but we expect to see similar effects as in NRT.

3. Concurrent use of cigarettes with NRT or ONPs. In a prior study from our group, large numbers of smokers concurrently smoked and used nicotine gum or other NRT products and the incidence of any significant AEs was < 1%. Recent research now demonstrates that starting nicotine patch prior to stopping smoking increases quit rates relative to starting patch at the time of cessation. With concurrent use of ONPs or traditional NRT with cigarettes, participants' nicotine intake may increase, risking nicotine overdose.

4. Use of ONPs/NRT among non-participants and non-smokers, including children. Whenever a product is given to a smoker to take home and use, there is potential that the product will be used by someone else, inclusive of non-smokers and even children. Such diversion has not been observed in an OSU Center for Tobacco Research’s ongoing R01 of e-cigarettes.

We ask established smokers exposed to tobacco and nicotine on a daily basis to sample either nicotine pouches (ONPs) or nicotine replacement therapy (NRT) products. ONPs may be less harmful to participants given the absence of tobacco. The NRT products are approved to aid in smoking cessation. Both products are available commercially. Because these products offer reduced risk and may be purchased by the participant commercially to reduce/eliminate tobacco consumption, these interventions do not represent greater than minimal risk to the participant. All other study assessments - collecting iCO data, surveys, and phone calls - are not much different than a normal quitline or clinic for smokers. As such, we do not believe this study represents greater than minimal risk to participants.

**Risk Mitigation**

While this trial is not without risk, every effort will be taken to reduce risk and undue burden on participants.

To minimize the risk of side effects from the study products:

- Participants will be provided with detailed instructions on the proper use of oral nicotine pouches and NRT.
- Participants will receive education on the potential risks and benefits of using oral nicotine pouches and NRT.
- Any adverse events or side effects experienced by participants will be documented and reported in accordance with the study protocol.

Nicotine pouches and traditional NRT do not seem to have the same potential harms of cigarettes and are available commercially; therefore, we believe participants are not at an elevated risks for sampling these products and may even benefit from the reduced tobacco intake during the switching phase. Because nicotine pouches only contain nicotine, and traditional NRT products such as lozenges and nicotine patches may help people quit or switch, we believe these products are not introducing increased harm. Knowledge gained from this trial will demonstrate best practices and the feasibility of switching to these products as a cigarette smoker, which is knowledge that is critical as these ONPs saturate the tobacco and nicotine market.

1a & 1b: Use of nicotine replacement therapy: We will exclude individuals based on standard FDA contraindications for NRT use (pregnancy, recent cardio trauma). Participants will be encouraged to contact the Study PI as soon as possible for serious AEs and for those conditions that OTC labeling suggests seeing a provider. We will withdraw participants who have a serious AE. For other AEs, the participant may be withdrawn from the study. We will also form a Data Safety and Monitoring Board. If the percent of serious or severe AEs appears to be greater than 5% this board will be notified to make a decision on early termination of the study.

2: Use of ONPs: Participants will be screened for general medical precautions and all participants will be monitored for adverse events during the study period. We will clearly advise against use of any tobacco product during pregnancy and breastfeeding and will exclude participants who are pregnant or breastfeeding. Participants will be educated about potential risks of tobacco use, including risks specific to ONPs, and concurrent use of these products with cigarettes. Any serious or unexpected adverse events will be reported to the IRB.

3. Our accompanying brochures will discuss the anticipated negative consequences of nicotine intoxication (nausea, headache) and advise participants to discontinue one or both products should they arise. We will track adverse events at every study contact and will have a toll-free number available for participants to call if they experience an adverse event (AE). All study contacts will remind participants of this number. Participants will be encouraged to contact Drs. [name] or [name] as soon as possible for serious events. If they wish, they may contact their local MD. We will withdraw participants who have a serious AE, become pregnant, or begin breastfeeding. For other AEs, if the participant’s physician or the participant wishes it, the participant will be withdrawn from the study. We will assess dependence on all products used, and for participants whose dependence increases for any product without a corresponding decrease >50% in CPD, we will refer them to seek treatment for tobacco dependence.

4. Use of ONPs/NRT among non-participants and non-smokers, including children: We will strongly advise participants that they are not to share the study product with others, and that they should store the product in a secure area that is out of reach of children and pets.

5. Confidentiality: We will use the participant’s name only in the screening and participant phone calls. All other references to participant data will be under a code. All database files will include password protection to further ensure confidentiality. We do not expect this study to present greater risks than other studies our team has conducted and expect to continue treating participant data with the utmost respect and confidentiality.

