**Research Design**

We will use a 6-month, two-arm, remote randomized switching trial of 1,000 smokers living in rural Appalachia. After randomization to the ONP or NRT (patch and lozenge) arm, during a 2-week Sampling Phase, participants will be sent ONPs or NRT in varied flavors and nicotine concentrations. Participants will sample and familiarize themselves with use of their study product and will select a nicotine concentration and flavor to use for the switch phase. During the 12-week Switch Phase, participants will attempt to stop smoking cigarettes and entirely switch to their study ONP or NRT. During the 14-week Observation Phase, participants will no longer receive study products but will be followed to evaluate longer-term switching outcomes. Throughout the trial, self-reported changes in cigarette smoking via online surveys will be confirmed using remote carbon monoxide assessment.

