## Observation Phase

The Observation Phase will begin immediately after the Switching Phase and will last for 14 weeks. The goal of the Observation Phase is to assess changes in smoking and sustained use of study products when they are no longer provided for free. Secondary goals will include assessing changes in nicotine concentrations, flavors, and brands used, as well as uptake of the other nicotine/tobacco products. This phase will help us to continue to track any adverse events that may occur following use of the study products.

Observation Phase: Survey

Participants will complete a survey at the end of the Observation Phase. ***(Survey Message, Observation Survey)*** The Observation Phase Survey will measure smoking and product use outcomes as described in the previous paragraph, including an iCO assessment. It will be delivered via REDCap and participants will receive several automated notifications to complete the survey. Study staff will also call, email, or text (any combination based on participant preferences) participants up to 10 times to remind them to complete the survey if they have not completed it within two weeks ***(Survey reminder).***

Observation Phase: Phone Call

After the survey is submitted, participants will receive a debriefing call. ***(Debrief Call Schedule Reminder)*** During the Debriefing Call, participants who report continued cigarette smoking will be strongly advised to quit smoking and will be emailed cessation resources ***(Cessation Resources).*** Those who have completely switched to ONPs or NRT will be encouraged to continue not smoking cigarettes and will be emailed cessation resources to assist with quitting all nicotine. ***(Debrief Phone Call Script)*** If we are unable to reach the participant by phone, they will receive a debrief email ***(Debrief Email).***

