## Subject Completion, Withdrawal, and Early Termination

Participants will be invited to complete a 29-week, fully-remote study involving baseline, sampling, switching, and observational phases. The participant timeline will be complete once the Observation Phase Survey and Debriefing Calls are complete. Participants have the option to withdraw at any point by expressing their desire to withdraw to study staff orally or in writing. Study staff will complete a withdrawal form to document this event. If at any point a participant becomes unable to complete study tasks per protocol (e.g., inconsistent responses reported on questionnaires; inability to provide iCO or survey responses; injury, illness, or medications that impair ability to accurately complete study measures; desire to quit tobacco use; or inappropriate behavior toward study staff), [name] reserves the right terminate a subject’s participation in the study based on their safety and ability to complete the protocol.

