Aim 3: Aim 3 will examine differences between the ONP and NRT arms in (H3a) abstinence from cigarettes, (H3b) number of days the study products are used, and (H3c) purchase and continued use of the study products during the 14-week Observation Phase. Hypothesis 3a: The analysis of abstinence from cigarettes at the end of the Observation Phase will mirror that of hypothesis 1b and will be evaluated with a logistic regression model. Hypothesis 3b: Linear regression analysis will be used to compare the number of days the products are used during the Observation Phase between the ONP and NRT arms; a normalizing transformation will be employed if needed and appropriate baseline characteristics will be adjusted for. Hypothesis 3c: The continued purchase and use of either ONP or NRT after during the 14-week Observation Phase will be compared between the arms with logistic regression analysis, adjusting for all appropriate confounders. Missing Data: In the event of missing data, we will contact participants immediately. If a participant drops out, we will attempt to gather follow-up information by calling and trying to reach the participant through other provided contact information. However, if a participant refuses to be contacted or loses contact with the investigators, we will censor data at point of loss. Two statistical approaches will be used to handle missing data. First, we will use inverse probability weighting with propensity scores. This is a two-step procedure in which we first model the probability of missingness as a function of baseline covariates and previous outcomes. Next, the inverse of the resulting predicted probabilities (from the logistic regression model) will serve as weights in our proposed model of the response. We will compare these results to a more conservative intent-to-treat approach as a final step.

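### Mandatory withdrawal after a serious AE, pregnancy or breastfeeding ends scheduled follow-up, when only the study product needs to stop

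*Protocol*

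**What the plan says.** The rule appears twice in Protocol section 13, Risk Mitigation. Items 1a & 1b (NRT) state: "We will withdraw participants who have a serious AE. For other AEs, the participant may be withdrawn from the study". Item 3 (concurrent use) states: "We will withdraw participants who have a serious AE, become pregnant, or begin breastfeeding". It then says that for other AEs, at the wish of the participant or the participant's physician, "the participant will be withdrawn from the study". Neither version requires the event to be related to product, and neither names a phase.

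Section 3 (Subject Completion, Withdrawal, and Early Termination) lets the investigator end a subject's "participation in the study based on their safety and ability to complete the protocol". It describes no follow-up afterwards.

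Other text points towards continued observation. In the Observation Phase "participants will no longer receive study products but will be followed to evaluate longer-term switching outcomes", and section 3 says of that phase: "This phase will help us to continue to track any adverse events that may occur following use of the study products". Risk Mitigation item 2 says "all participants will be monitored for adverse events during the study period". Item 3 ties AE collection to study contacts.

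**The concern.** The rule protects the participant by ending exposure, which is right. Read with its neighbouring sentences, it also ends observation, which is not needed for protection. Two things are lost.

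- **Safety.** The event is recorded and reported, but the scheduled occasions for seeing how it resolves, or whether another follows, disappear. This falls on the participants whose course matters most, including anyone who becomes pregnant after ONP exposure. Section 13 acknowledges that ONP use in pregnant women has not been studied.
- **Outcome data.** The primary outcome needs a survey and an iCO reading at week 12. For these participants it would be missing because of a safety event after randomisation, although it could be collected remotely. The weighting model in section 15 uses baseline covariates and previous outcomes; it does not name safety events as predictors of missingness.

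A serious AE in the Observation Phase shows the problem most clearly. The study no longer supplies product, so withdrawal would end only the follow-up.

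**Working it through.** **1. What withdrawal ends**

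| Place in Protocol | Trigger | What stops |
|---|---|---|
| Section 13, opening paragraph | Palpitations, severe chest pain, allergic reaction, overdose symptoms and similar | Product; medical care advised; leaving the study not mentioned |
| Risk Mitigation item 3, brochures | Nicotine intoxication | One or both products |
| Risk Mitigation items 1a & 1b, and item 3 | Any serious AE; item 3 adds pregnancy and breastfeeding | The participant is withdrawn; the next sentence in each says from the study |
| Section 3, termination clause | Safety or inability to complete tasks | Participation in the study |

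The protocol has wording for stopping product alone and does not use it for the three mandatory triggers. Since AEs are tracked at contacts and abstinence needs survey plus iCO, ending participation removes both.

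**2. Contacts lost** (section 3, Participant Timeline)

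- Withdrawn just after the switch date: mid-switch, post-switch and observation surveys, each with iCO (3 × 25 = 75 min), plus the mid-switch and debrief calls (2 × 10 = 20 min). Total 95 min.
- Withdrawn just after the post-switch survey: one survey with iCO and one call (25 + 10 = 35 min).

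**3. Number affected**

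The protocol gives no expected rate. The nearest figure is in section 13, Additional details, item 3: significant AEs below 1% in an earlier study of smoking with concurrent NRT. Significant is not the same as serious, so its use here is an assumption.

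- Serious AEs: below 0.01 × 1,000 = 10.
- Follow-up from the start of sampling: 2 + 12 + 14 = 28 weeks. If events are spread evenly (assumption), 14/28 = half, or fewer than 5, precede the week-12 outcome.
- Planned loss by week 12: 1,000 − 800 = 200. So 5/200 = 2.5% of that loss at most.
- Pregnancy: assumed 0% to 1% of about 500 women, giving 0 to 5. Section 5 excludes anyone planning pregnancy within 6 months. New breastfeeding is very unlikely and is not counted.

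**4. Power**

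Inputs from section 15: 13% vs 23%, two-sided α = 0.05, chi-squared test.

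Power = Φ{[0.10√n − 1.96√(2 × 0.18 × 0.82)] / √(0.13 × 0.87 + 0.23 × 0.77)}, with n per arm.

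- n = 400: Φ[(2.000 − 1.065)/0.539] = 95.9%. The plan says above 95%: reproduced.
- n = 350: Φ[(1.871 − 1.065)/0.539] = 93.3%. The plan says above 90%: reproduced.
- Extra loss of 1% of the 500 per arm (10 in total, all taken as before the assessment): n = 395 gives 95.7%; n = 345 gives 92.9%.
- Extra loss of 2% (20 in total, more than the 10 + 5 above): n = 390 gives 95.4%; n = 340 gives 92.6%.

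**5. Effect on the primary difference**

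Suppose missing counts as smoking, which the protocol does not state, and 23% and 13% apply to those retained.

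- With the planned 80% retention: 23 × 0.80 − 13 × 0.80 = 18.4 − 10.4 = 8.0 points.
- Widest split of the serious AEs: all 10 in one arm (2% of 500), half of them before week 12 (1%).
- All in ONP: 23 × 0.79 − 10.4 = 18.17 − 10.4 = 7.77 points.
- All in NRT: 18.4 − 13 × 0.79 = 18.4 − 10.27 = 8.13 points.

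The shift is at most about 0.2 points.

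**The case against.** The strongest reply is that the rule does not itself say what ends, and that other text keeps these participants in view. Section 15 says: "If a participant drops out, we will attempt to gather follow-up information by calling". It censors only those who refuse contact or lose contact. The statement about monitoring all participants can be read as continuing after withdrawal. Serious events go to the IRB, a Data Safety and Monitoring Board is to be formed, a toll-free AE number exists, and operational detail is left to a procedure manual that is not shown.

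Part of this stands. Some contact with withdrawn participants is possible, and the event itself is reported. But the section 15 text addresses dropout and loss of contact, does not clearly cover withdrawal imposed by the study, and does not preserve scheduled iCO or AE contacts. The toll-free number depends on the participant calling. IRB reporting records the event, not its later course. A manual should not have to override an unqualified protocol rule. Nor can an SAP restore data that the protocol has stopped collecting.

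Three stronger readings are tempting and not supported:

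- **That the protocol never separates stopping product from leaving.** It does, for warning symptoms and intoxication in section 13.
- **That these participants leave the analysis set.** The note under Inclusion/Exclusion Criteria defines the intent-to-treat sample by baseline completion, iCO confirmation and, where applicable, non-pregnancy at the pre-sampling call. Later withdrawal does not remove anyone.
- **That serious AEs would go unreported.** Documentation and IRB reporting are provided for.

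**Conclusion.** The point holds as a minor design fault. The protocol fixes a mandatory rule that, on its most natural reading, ends scheduled safety and abstinence assessment for participants with a serious AE, pregnancy or breastfeeding. That runs against its own statements on AE tracking and monitoring.

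The size is probably fewer than about 10 of 1,000 for serious AEs, fewer than 5 of them before week 12, plus perhaps 0 to 5 pregnancies. This rests on three assumptions: that the below-1% figure carries over to serious AEs in both arms, that events are spread evenly over 28 weeks, and the assumed pregnancy range. A reader might infer a threat to power or to the primary result; the figures above do not support that. What is at stake is safety follow-up and a small amount of avoidable missing data whose cause is a safety event.

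**What to change.** In Risk Mitigation items 1a & 1b and item 3, replace withdrawal with permanent discontinuation of study product for serious AEs, pregnancy and breastfeeding. State that, unless the participant withdraws consent, the scheduled remote surveys, iCO tests and AE contacts continue to the end of the Observation Phase. Make the same distinction in section 3, Subject Completion, Withdrawal, and Early Termination. Stopping product should remain mandatory after a serious AE, so that the existing protection is not relaxed.

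**Cost.** Beyond the wording, the contacts are already scheduled and remote. Per participant from just after the switch date:

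- at most 95 minutes of contact;
- up to 3 × $25 + $25 = $100 in incentives;
- up to 10 reminder contacts for each of three surveys.

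For 10 participants, staff time on calls is 10 × 20 = 200 minutes (about 3.3 hours), before reminders. Continued assessment of participants who become pregnant may need a check with the IRB, because section 5 calls for an appendix when pregnant women are intentionally studied.
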